# Consolidative use of radiotherapy to block oligoprogression in patients with metastatic melanoma on Systemic Therapy (CURB-Melanoma) - a single arm, phase 2 clinical trial

**DOI:** 10.3389/fonc.2026.1841070

**Published:** 2026-07-06

**Keywords:** immunotherapy, metastatic melanoma, oligometastatic disease, oligoprogression, SBRT

## Abstract

**Purpose/objective:**

Patients with metastatic melanoma on active systemic therapy can develop isolated disease progression while the majority of disease remains controlled (oligoprogression). This phase 2 trial investigates whether stereotactic body radiation therapy (SBRT) or hypofractionated radiation to oligoprogressive sites can improve progression-free survival (PFS) in metastatic melanoma patients receiving first-line systemic therapy.

**Materials/methods:**

This is an open-label, single-arm phase 2 trial. Eligible patients have metastatic melanoma with ≤10 extracranial oligoprogressive sites while on first-line systemic therapy. Oligoprogression is defined using modified RECIST 1.1 or PERCIST criteria. All oligoprogressive sites will receive SBRT per institutional guidelines, typically delivered over 3 fractions. Patients will stay on current systemic therapy. The primary endpoint is PFS defined as the time from enrollment to the date of further disease progression. Secondary endpoints include overall survival, time on current systemic therapy, out-of-field response, tolerance of SBRT, and quality of life (QOL). In addition, serial blood samples are collected for exploratory analyses of circulating tumor DNA (ctDNA), mutant allele fraction, and immune profiling (including CD8+ T-cell subsets). The trial aims to enroll 52 patients over 12 months with additional 24 months of follow-up.

**Discussion:**

This trial will evaluate the impact of SBRT on further disease progression, treatment tolerance, and blood-based immune and molecular correlatives in patients with oligoprogressive metastatic melanoma. Findings may help define the standard of care for managing oligoprogression during first-line systemic therapy.

**Clinical trial registration:**

## Introduction

Oligoprogression is characterized by the progression of cancer at a limited number of sites while majority of the disease remains stable on systemic therapy. Management of oligoprogressive disease may involve either switching systemic therapy or incorporating local treatments such as ablative stereotactic body radiotherapy (SBRT) or hypofractionated radiotherapy, while continuing or modifying the existing systemic regimen.

Prospective data supporting the benefit of SBRT for oligoprogressive cancers are scarce, and no trial has specifically evaluated patients with metastatic melanoma on immunotherapy (1–6). The recently published results of the CURB trial (randomized, phase II) clearly showed a four-fold improvement progression-free survival (PFS) with the addition of SBRT for patients with metastatic non−small cell lung cancer (mNSCLC). The clinical observation was accompanied by a corresponding decrease in mutant allele fraction of circulating tumor DNA (ctDNA) fraction in these patients after SBRT (7). Aside from CURB, another randomized phase 2 trial of SBRT for oligoprogressive cancers of mixed histologies was recently published. The STOP trial randomized patients to either SBRT or continuing standard-of-care (SOC) treatment, but was found negative (6). Thus far, there has been no trial investigating the effect of SBRT in oligoprogressive melanoma.

Melanoma incidence is increasing in Canada and worldwide (8–10). In 2022, an estimated 331,647 persons worldwide were diagnosed with melanoma, and approximately 58,645 persons died of the disease (11).

Although most patients are diagnosed with local disease and are cured with surgical resection, some patients develop or present with metastatic disease. Over the past decade, systemic treatment for metastatic melanoma has changed substantially. For example, the recently published 10-year survival outcomes from the Checkmate-067 trial demonstrated a 10-year mOS of 71.9 months for the combination of nivolumab and ipilimumab, and 37 months of nivolumab monotherapy. The 1- and 2-year PFS were about 50% and 45% respectively (12). For patients who progressed on immunotherapy, treatment options are limited. For patients harboring BRAF V600 mutations, a dual BRAF/MEK inhibitors are considered SOC, with a median PFS (mPFS) of about 10 months (13). Wild-type patients are treated with TIL (tumor infiltrating lymphocytes) therapy, resulting in a mPFS of 7 months (14).

CURB-Melanoma is designed to prospectively assess whether SBRT extends PFS in this population.

## Methods and analysis

### Study design, outcomes and end-points

CURB-Melanoma is an investigator-initiated, prospective, single-arm phase II clinical trial being conducted at the Princess Margaret Cancer Centre, University Health Network, Toronto, Canada. The trial is enrolling patients with metastatic melanoma who exhibit oligoprogression on first-line therapy (see **Figure 1** for trial schema).

**Figure 1 f1:**
[figure not shown]
CURB-Melanoma Trial Schema.

Primary Endpoint:

Progression-free survival - defined as time from enrollment to further disease progression (assessed by modified RECIST) or death from any cause.

Secondary Endpoints:

Overall survival - defined as the time from study enrollment to death from any cause.Time on current systemic therapy before switching to second line therapy - captures the duration from initiation of the current systemic therapy to the start of second-line treatment.Toxicity - treatment-related adverse events will be assessed and graded according to CTCAE v5.0.Quality of life - patient-reported outcomes will be evaluated using validated instruments (PRO-CTCAE, EORTC-QLQ-C30).

Exploratory Endpoints:

Out of field response - defined as a new radiographic response (per RECIST 1.1) in a non-irradiated lesion that was stable at enrollment. This endpoint is hypothesis-generating, as attribution to an abscopal effect is limited by the concurrent influence of ongoing systemic therapy.Blood collection: at baseline, 4 weeks post-radiation, and at the time of progression. At each timepoint, two 10 mL Streck Cell-Free DNA Blood Collection Tubes (BCT) will be collected for future analysis of circulating tumor DNA (ctDNA), cytokines, proteomics, metabolomics, and other serum/plasma biomarkers. In addition, two 10 mL Cell Preparation Tubes (CPT) with sodium citrate will be collected for isolation of peripheral blood mononuclear cells (PBMCs) for multiplex analysis of circulating immune cells including, flow cytometry (CyTOF), T cell receptor sequencing (TCR-seq) and single-cell RNA sequencing (scRNA-seq) for a minimal volume of 40 mL.

The primary hypothesis is that adding SBRT or hypofractionated radiotherapy to oligoprogressive lesions while continuing systemic treatment will yield a clinically meaningful extension of PFS. The trial protocol has been approved by the institutional Research Ethics Board, and the study will be monitored by the center’s clinical trials unit for compliance and safety.

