### Participant eligibility

Participants must be adults (age ≥18) with an ECOG performance status of 0-2, who have histologically confirmed metastatic melanoma. Patients must be receiving first-line systemic therapy and have demonstrated oligoprogressive disease on restaging evaluations. Oligoprogression is defined in this study as the presence of ≤10 sites of progressive disease (new or enlarging metastases) detected on imaging, while all other disease sites remain stable or responding to therapy. All progressive lesions must be extracranial (patients with only brain progression are excluded) and deemed safely treatable with high-dose radiotherapy.

Inclusion criteria include:

Metastatic melanoma on first-line systemic therapy: patients may be on anti-PD-1 monotherapy/combination (e.g. nivolumab ± ipilimumab), or on BRAF inhibitors.Oligoprogressive disease with ≤10 progressing lesions: progression is defined per modified RECIST 1.1 (≥20% diameter increase) or PERCIST (metabolic progression on PET) criteria for each lesion​. New lesions (≥5 mm) count toward the total of 10​. There is no upper limit on the total number of metastases in the body, as long as at most 10 are progressing.Amenable to SBRT: the locations of progression must be such that radiotherapy can be delivered without undue risk (assessed by a radiation oncologist). Lesions previously irradiated can be retreated if safe, and prior palliative radiation is permitted.Ability to consent and comply: patients must be willing and able to provide informed consent and comply with study procedures, including completion of quality-of-life questionnaires.

Exclusion criteria include:

Having >10 progressive lesions (widespread progression).Untreated or symptomatic central nervous system disease (patients with leptomeningeal disease are excluded​, as are those with unstable or symptomatic brain metastases).Pregnancy, or any serious comorbidity that would contraindicate radiotherapy (such as certain radiosensitive genetic conditions like ataxia-telangiectasia or scleroderma)​.Patients in whom prior radiation to a site precludes safe re-irradiation.Any circumstance that, in the investigator’s judgment, would interfere with the patient’s ability to participate or with the study results (such as significant psychosocial barriers to follow-up).

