Treatments are delivered using image-guided radiotherapy on dedicated linear accelerators. SBRT to multiple lesions may be given sequentially or concurrently, at the discretion of the treating radiation oncologist, but the aim is to complete radiation to all sites as soon as feasible, preferably within two weeks of enrollment. Radiation therapy is typically given during the “off week” of systemic therapy to avoid treatment interruption; this timing is logistical rather than biological, and no drug holiday is planned. Thus, patients continue on their systemic treatment beyond progression, with the intent that eliminating the resistant lesions will allow the systemic treatment to remain effective for the other sites. All radiotherapy and medical oncology interventions in this study are standard modalities - SBRT is an established technique, and the drug regimens are the current standard of care for first-line treatment. Supportive care is provided as needed, and any toxicity from radiation or systemic therapy is managed per usual clinical practice.

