### Statistical analysis

As reviewed in the literature, first-line therapy with immune checkpoint inhibitors results in a mPFS of 11.5 months (12). Our study was designed with the expectation that we would observe a median PFS improvement of about 7 months with addition of SBRT. Assuming an enrolment time of 12 months and follow-up of 24 months, 15% drop out and another 15% of screen failure, a sample size of 52 patients will achieve 85% power at 0.05 significance level to detect a median PFS of 7 months based on a two-sided, single arm log-rank test.

PFS/OS will be estimated using Kaplan-Meier (KM) method and presented graphically. The cumulative incidences of change in systemic therapy and acute/late toxicity will be estimated using the Aalen-Johansen method, where mortality without events of interest will be treated as competing event. Univariate Cox proportional hazard models will also be conducted to examine the association of PFS/OS with patient and tumor characteristics of interest, such as age, sex and the number of oligoprogressive lesions treated, BRAF mutational status, and type of first-line systemic therapy. Similarly, the univariate Fine-Gray competing risk models will be applied to examine the association of time to change in systemic therapy/acute/late toxicity with the patient and tumor characteristics of interests. Multivariable analyses (MVA) will also be conducted to determine the association if applicable. The change in QOL scores at follow ups from baseline (before SBRT) will be analyzed using linear mixed-effect models and the change in scores of >10 points would be deemed a minimal clinically important difference. The other categorical secondary outcomes (e.g. Out of field response, AE) will be summarized using frequency counts and proportion.

An interim analysis will be conducted after the first 25 patients have been enrolled and followed for at least 6 months, to assess safety and early efficacy trends. If ≥30% of patients experience grade 3 or higher toxicities deemed related to SBRT at that time, early termination of the trial will be considered.

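### Time on current systemic therapy is counted from the start of that therapy, so it includes pre-enrolment time in which neither a switch nor a death can occur

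*Protocol article*

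**What the plan says.** All references are to the protocol article.

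- **Endpoint definition** (Study design, outcomes and end-points, Secondary Endpoints): time on current systemic therapy "captures the duration from initiation of the current systemic therapy to the start of second-line treatment".
- **The other time-to-event endpoints** (same section): PFS is "defined as time from enrollment to further disease progression (assessed by modified RECIST) or death from any cause", and OS is "defined as the time from study enrollment to death from any cause". Both start at enrolment.
- **Entry condition** (Participant eligibility): "Patients must be receiving first-line systemic therapy and have demonstrated oligoprogressive disease on restaging evaluations".
- **Timing of radiotherapy** (Treatment intervention): it follows enrolment, with completion at all sites "preferably within two weeks of enrollment".
- **Analysis** (Statistical analysis): "The cumulative incidences of change in systemic therapy and acute/late toxicity will be estimated using the Aalen-Johansen method". Death before the event counts as a competing risk. For regression on patient and tumour characteristics, "the univariate Fine-Gray competing risk models will be applied to examine the association of time to change in systemic therapy/acute/late toxicity". This section gives no time origin of its own and mentions neither delayed entry nor a landmark.

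**The concern.** The definition starts the clock at a point that every enrolled patient has, by the eligibility rule, already survived without switching treatment. A standard cumulative incidence estimate from that point counts patients as at risk before they could have been observed to fail. The early part of the curve is flat by design, and the duration read from it contains time that SBRT could not have influenced.

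The regression has a related problem. One named covariate is the number of oligoprogressive lesions treated, which is known only at or after enrolment. If time from therapy start is regressed on it, its association is mixed with how long the patient had been treated before entering the trial.

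The Discussion argues that ablating oligoprogressive sites prolongs the use of first-line therapy, and this endpoint is the one that would show it. As defined it would look long even if SBRT did nothing, and it could not be set beside the trial's own PFS.

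**Working it through.** No sample size, power or benchmark is stated for this endpoint, so there is no figure to reproduce. The check has a logical step and an illustration of size.

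**Step 1: decompose the endpoint.** For an enrolled patient let W be the time from initiation of current therapy to enrolment, and T the time from enrolment to second-line therapy. The endpoint as defined is W + T.

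- During W a switch is impossible, because the patient must still be on first-line therapy at entry.
- During W the competing event is impossible, because the patient must be alive at entry.
- SBRT can affect T only, because it is given after enrolment.

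So W adds to the endpoint in full and carries no information about SBRT. This follows from the definition and the entry rule alone.

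**Step 2: inputs for size.**

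- *T:* median 5 months, an assumption. The Discussion cites this as the median time to change treatment in a retrospective SBRT series of 69 patients, 29 of them with oligoprogression. It does not give that series' time origin or say whether the figure applies to the 29.
- *W:* not given anywhere, and assumed to be 3 to 12 months. The article's imaging interval of roughly 12 weeks and its cited first-line median PFS of 11.5 months make this range reasonable but do not establish it.
- Competing death is ignored for simplicity.

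**Step 3: constant W.** Then median(W + T) = W + median(T), and the share before enrolment is W / (W + 5).

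| W (months) | Endpoint median (months) | Share before enrolment |
|---|---|---|
| 3 | 3 + 5 = 8 | 3/8 = 38% |
| 6 | 6 + 5 = 11 | 6/11 = 55% |
| 9 | 9 + 5 = 14 | 9/14 = 64% |
| 12 | 12 + 5 = 17 | 12/17 = 71% |

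**Step 4: W varying between patients.** With T exponential (median 5 months) and W exponential with median 3, 6, 9 or 12 months, simulation with 400,000 draws gives a median of W + T of about 9.5, 13.3, 16.7 and 19.8 months. A constant lead time therefore does not exaggerate the effect on the median.

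**Step 5: same patients, clock started at enrolment.** The median is 5 months in every row, because W no longer enters.

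**The case against.** The strongest reply is that the analysis origin is inferred. The Statistical analysis section states none. It handles change of systemic therapy in the same sentences as acute and late toxicity, which can sensibly be counted only from enrolment or radiotherapy. Assessments and follow-up also says that subsequent therapies are recorded to analyse time to next treatment, again without an origin. A post-enrolment clock may be intended, and delayed entry is a detail that an article may leave to an analysis plan not shown here. The endpoint's name also matches its definition, and total treatment duration is a legitimate descriptive quantity.

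Part of this stands. The bias in the Aalen-Johansen and Fine-Gray results follows only if those methods use the origin that the endpoint definition gives. But that is the only origin printed for this outcome. It is stated expressly rather than left out, and a different origin in the analysis would contradict it. The descriptive reading is not offered either: the endpoint carries no such label, whereas out-of-field response, in the same section, carries an explicit caution about concurrent systemic therapy.

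A reader might go further and infer that the plan credits the pre-enrolment time to SBRT. The article does not support that. This endpoint has no comparator, threshold or test. The limitations paragraph of the Discussion says that SBRT's contribution to any PFS gain cannot be separated out in a single-arm trial, and that outcomes are to be read as generating hypotheses. That paragraph does not mention the lead time in this endpoint, but it does count against a claim of attribution. Nor is this the endpoint on which the trial stands: the primary hypothesis concerns PFS.

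**Conclusion.** Wrong as written, for one secondary endpoint. The stated origin puts guaranteed event-free, pre-SBRT time into the outcome and differs from the enrolment origin of PFS and OS. That the duration is lengthened is certain from the definition and the eligibility rule. The distortion of the cumulative incidence and Fine-Gray estimates follows if they use the printed origin without delayed entry.

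The size is not known. The range of 8 to 17 months, with 38% to 71% before enrolment, rests on an assumed constant lead time of 3 to 12 months and an assumed post-enrolment median of 5 months. It should be quoted only as an illustration. The primary PFS analysis and its sample size are unaffected.

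**What to change.** Define the endpoint as time from enrolment to start of second-line therapy, with death before a switch as the competing event, and fit the Fine-Gray models on that time scale. It then has the same origin as PFS and OS.

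If total duration since initiation of first-line therapy is also of interest, estimate it with delayed entry at enrolment, label it descriptive, and report the pre-enrolment duration separately. Delayed entry corrects the risk sets; it does not turn total duration into a measure of SBRT.

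State the chosen origin in the Statistical analysis section as well, so that definition and method agree.

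The cost is a changed line in the endpoint definition and one in the analysis text. The dates of initiation, enrolment and start of second-line therapy are already needed for the endpoints as they stand, so no new data are required.

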### Participant eligibility

Participants must be adults (age ≥18) with an ECOG performance status of 0-2, who have histologically confirmed metastatic melanoma. Patients must be receiving first-line systemic therapy and have demonstrated oligoprogressive disease on restaging evaluations. Oligoprogression is defined in this study as the presence of ≤10 sites of progressive disease (new or enlarging metastases) detected on imaging, while all other disease sites remain stable or responding to therapy. All progressive lesions must be extracranial (patients with only brain progression are excluded) and deemed safely treatable with high-dose radiotherapy.

Inclusion criteria include:

Metastatic melanoma on first-line systemic therapy: patients may be on anti-PD-1 monotherapy/combination (e.g. nivolumab ± ipilimumab), or on BRAF inhibitors.Oligoprogressive disease with ≤10 progressing lesions: progression is defined per modified RECIST 1.1 (≥20% diameter increase) or PERCIST (metabolic progression on PET) criteria for each lesion​. New lesions (≥5 mm) count toward the total of 10​. There is no upper limit on the total number of metastases in the body, as long as at most 10 are progressing.Amenable to SBRT: the locations of progression must be such that radiotherapy can be delivered without undue risk (assessed by a radiation oncologist). Lesions previously irradiated can be retreated if safe, and prior palliative radiation is permitted.Ability to consent and comply: patients must be willing and able to provide informed consent and comply with study procedures, including completion of quality-of-life questionnaires.

Exclusion criteria include:

Having >10 progressive lesions (widespread progression).Untreated or symptomatic central nervous system disease (patients with leptomeningeal disease are excluded​, as are those with unstable or symptomatic brain metastases).Pregnancy, or any serious comorbidity that would contraindicate radiotherapy (such as certain radiosensitive genetic conditions like ataxia-telangiectasia or scleroderma)​.Patients in whom prior radiation to a site precludes safe re-irradiation.Any circumstance that, in the investigator’s judgment, would interfere with the patient’s ability to participate or with the study results (such as significant psychosocial barriers to follow-up).

### Treatment intervention

Enrolled patients will undergo SBRT or single-fraction hypofractionated radiotherapy to all identified oligoprogressive lesions. The default dose for each oligoprogressive lesion will be 8–10 Gy x 3 fractions, or 8–10 Gy x 1 fraction but other variations are allowed if there are multiple lesions or different dose/fractionations are deemed safer and more feasible per treating physician. For details of planning guidelines please refer to the CURB2 trial protocol [NCT06686771]. Dose and fractionation are individualized per lesion to maximize tumor ablation while maintaining safety (all planned doses are within established normal tissue tolerance limits for SBRT, See **Table 1**).

**Table 1 T1:** Normal structure constraints and compliance criteria (3-fraction regimen).

Serial Tissue	Volume	Per Protocol (Gy)	Endpoint (≥ Grade 3)
Optic Pathway	D0.03cc[Gy]	<=17.4	Neuritis
	D0.2cc[Gy]	<=15.3	
Cochlea	D0.03cc[Gy]	<=20	Hearing loss
Brainstem (not medulla)	D0.03cc[Gy]	<=23.1	Cranial neuropathy
	D0.5cc[Gy]	<=18	
Spinal Cord and medulla	D0.03cc[Gy]	<=22.5	Myelitis
	D0.35cc[Gy]	<=18	
	D1.2cc[Gy]	<=13	
Cauda Equina	D0.03cc[Gy]	<=24	Neuritis
	D5cc[Gy]	<=21.9	
Sacral Plexus	D0.03cc[Gy]	<=24	Neuropathy
	D5cc[Gy]	<=22.5	
Esophagus	D0.03cc[Gy]	<=25.2	Stenosis/fistula
	D5cc[Gy]	<=17.7	
Brachial Plexus	D0.03cc[Gy]	<=26	Neuropathy
	D3cc[Gy]	<=22	
Heart/Pericardium	D0.03cc[Gy]	<=30	Pericarditis
	D15cc[Gy]	<=24	
Great vessels	D0.03cc[Gy]	<=45	Aneurysm
	D10cc[Gy]	<=39	
Trachea and Large Bronchus	D0.03cc[Gy]	<=30	Stenosis/fistula
	D5cc[Gy]	<=25.8	
Bronchus-smaller airways	D0.03cc[Gy]	<=30	Stenosis with atelectasis
	D0.5cc[Gy]	<=25.8	
Rib	D0.03cc[Gy]	<=36.9	Pain or fracture
	D1cc[Gy]	<=28.8	
Skin	D0.03cc[Gy]	<=33	Ulceration
	D10cc[Gy]	<=31	
Stomach	D0.03cc[Gy]	<=24	Ulceration/fistula
	D10cc[Gy]	<=21	
Bile duct	D0.03cc[Gy]	<=36	Stenosis
Duodenum	D0.03cc[Gy]	<=24	Ulceration
	D5cc[Gy]	<=15	
	D10cc[Gy]	<=11.4	
Jejunum/Ileum	D0.03cc[Gy]	<=27	Enteritis/obstruction
	D5cc[Gy]	<=16.2	
Colon*	D0.03cc[Gy]	<=30	Colitis/fistula
	D20cc[Gy]	<=20.4	
Rectum	D0.03cc[Gy]	<=30	Proctitis/fistula
	D20cc[Gy]	<=20.4	
Ureter	D0.03cc[Gy]	<=30	Stenosis
Bladder	D15cc[Gy]	<=15	Cystitis/fistula
Parallel Tissue	Constraint**	Per Protocol	Endpoint (≥ Grade 3)
Lungs-GTV	CV10.5Gy	>=1500cc	Basic Lung Function
	CV11.4Gy	>=1000cc	
	V20Gy	<=15%	Pneumonitis
	V11Gy	<=37%	
Liver	CV17.1GY	>=700cc	Basic Liver Function
Kidneys (Right & Left)	CV15Gy	>=200cc	Basic Renal Function

Treatments are delivered using image-guided radiotherapy on dedicated linear accelerators. SBRT to multiple lesions may be given sequentially or concurrently, at the discretion of the treating radiation oncologist, but the aim is to complete radiation to all sites as soon as feasible, preferably within two weeks of enrollment. Radiation therapy is typically given during the “off week” of systemic therapy to avoid treatment interruption; this timing is logistical rather than biological, and no drug holiday is planned. Thus, patients continue on their systemic treatment beyond progression, with the intent that eliminating the resistant lesions will allow the systemic treatment to remain effective for the other sites. All radiotherapy and medical oncology interventions in this study are standard modalities - SBRT is an established technique, and the drug regimens are the current standard of care for first-line treatment. Supportive care is provided as needed, and any toxicity from radiation or systemic therapy is managed per usual clinical practice.

